### 2.8. Primary Outcomes

The primary outcome of the study is the arrest of caries. The hardness of treated cavitated surfaces of teeth on probing (periodontal probe) is an indication that a lesion is arrested. Blackish discoloration of surface/cavity alone will not be a criterion for defining the arrested caries.

The outcome assessment will be performed for all the arms at 6 months and 12 months. SDF treated cavities of teeth with arrested caries are defined as surfaces with active cavitated caries at baseline that changed into surfaces with arrested cavitated caries on subsequent assessments. The possible scenarios and their assessment are as follows:Any teeth with treated carious lesions that are lost due to exfoliation will be considered arrested throughout the lifetime of the tooth. For any reason, if the child’s teeth are restored before the trial period, censoring of the data depends on the duration of the trial period the child has participated.The following dental complications due to the evolution of caries will not be considered as caries arrested.○The teeth extracted due to caries progression.○If the SDF treated cavities, caries progressed beyond the dentine.○If the tooth is extracted due to fracture, trauma will not be counted for the study.

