## 4. Statistical Methods

The outcome of the treated carious lesion is binary, either arrested lesion or failed to arrest at 6 months follow-up and at the end of 12 months follow up visit. The outcome will be assessed at two levels: Tooth-level—the proportion of cavitated surfaces at baseline will be compared with the proportion of the surfaces arrested at each frequency of application at 6 months follow-up and the end 12 months using chi-square methods. Between three frequencies of application (annual, semi-annual, and four times a year applications) the proportion of arrested surface at 6 months follow-up and end 12 months will be compared. This comparison will be stratified by type of tooth (posterior vs. anterior) and type of surfaces (facials vs. lingual). Child-level—each child may have one or more cavitated carious surface treated with SDF. So, the per-child proportion of cavitated carious lesions at baseline treated with 38% SDF applied at different frequencies that stayed arrested throughout observation will be determined.

The regression will be modelled on the dependent variable as a percentage of the arrested carious lesion per child with another. The two sets of analysis will be done, first, the intention-to-treat set, considering all patients as randomized regardless of whether they received the randomized treatment, and second, the “per protocol” analysis set. The hypothesis that four times application of 38% of SDF superior to other frequencies (annual or semi-annual application) is accepted, only if shown to be superior using both the “intention to treat” and “per protocol” analysis sets.

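### Shed teeth are scored as arrested whatever probing last showed, and restored teeth are censored although the named analyses cannot use censored lesions

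*Protocol article*

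**What the plan says.** Section 2.8 (Primary Outcomes) sets the criterion: "The hardness of treated cavitated surfaces of teeth on probing (periodontal probe) is an indication that a lesion is arrested". Success is then defined by change between examinations, as "surfaces with active cavitated caries at baseline that changed into surfaces with arrested cavitated caries on subsequent assessments", with assessments at 6 and 12 months in every arm.

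The same section lists special cases:

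- Exfoliation: "Any teeth with treated carious lesions that are lost due to exfoliation will be considered arrested throughout the lifetime of the tooth". No condition is placed on what probing last found.
- Restoration, whatever the reason: "censoring of the data depends on the duration of the trial period the child has participated".
- Not arrested: "The teeth extracted due to caries progression", and also lesions that have progressed past the dentine. Restoration is not on this list.

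Section 4 (Statistical Methods) says: "The outcome of the treated carious lesion is binary, either arrested lesion or failed to arrest at 6 months follow-up", and again at 12 months. The tooth-level comparison uses chi-square methods. The child-level outcome is the share of a child's treated lesions that remained arrested over the whole of follow-up, and the regression takes the percentage arrested per child as its dependent variable. No time-to-event method is named.

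**The concern.** The exfoliation rule replaces an examination with an assumption, and the assumption always favours success. It can overwrite a recorded failure: a lesion found active at 6 months becomes arrested at 12 months because the tooth has gone. That contradicts the probing criterion, and it also sits badly with the child-level outcome in Section 4, which asks whether lesions remained arrested throughout.

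The restoration rule has a different fault. Censoring means something in a time-to-event analysis. It has no meaning in a chi-square table at a fixed visit or in a per-child percentage. A lesion restored between 6 and 12 months can keep its 6-month result but has no defined 12-month result. Some of these lesions will have been restored because the caries stayed active or advanced. The same clinical course ending in extraction would count against the arm.

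At stake are the reported arrest percentages, the size of the difference between arms and, if restoration is more common in one arm, the validity of the comparison. Section 2.12 makes differential restoration possible: the operator applying SDF is not blinded, and routine restoration is an available treatment at the centre. Blinded assessors cannot correct for lesions they can no longer probe.

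**Working it through.** **Inputs from the protocol article.** Planned difference 14 percentage points and 120 children per arm before allowance for loss (Section 2.11); age 2–6 years at entry (2.5.1); teeth nearing exfoliation excluded (2.5.2); 12 months of follow-up (2.10). No exfoliation rate, restoration rate or base arrest rate is stated, so there is no figure of the plan's own to reproduce on this point. The 120 per arm cannot be derived without a base rate; that is a separate matter and nothing below depends on it.

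**Assumptions.** True arrest 70% versus 84% (a 14-point gap), the same exfoliation share *e* for arrested and active lesions, and, for restoration, a share *r* of non-arrested lesions restored and left without a result. Power is for a two-sided 5% test with 120 per arm and one outcome per child.

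**Exfoliation scored as arrested.** Observed proportion = (1 − e)p + e, so each arm rises by e(1 − p) and the difference is multiplied by (1 − e).

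| e | lower arm | upper arm | difference (points) | power |
|---|---|---|---|---|
| 0 | 70.0% | 84.0% | 14.0 | 73.4% |
| 2% | 70.6% | 84.3% | 13.7 | 72.3% |
| 5% | 71.5% | 84.8% | 13.3 | 70.5% |
| 10% | 73.0% | 85.6% | 12.6 | 67.5% |

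The shrinkage in points does not depend on the assumed base rate: 14 × 0.98 = 13.7 and 14 × 0.90 = 12.6.

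**Restored failures without a result, same share in both arms.** Observed proportion = p / [1 − r(1 − p)].

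- r = 10%: 0.70/0.97 = 72.2%; 0.84/0.984 = 85.4%; difference 13.2 points.
- r = 20%: 0.70/0.94 = 74.5%; 0.84/0.968 = 86.8%; difference 12.3 points.
- r = 30%: 0.70/0.91 = 76.9%; 0.84/0.952 = 88.2%; difference 11.3 points.

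At r = 20% the difference is 13.1 points if the true rates are 56% versus 70%, and about 12.0 points if they are 75% versus 89%.

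**Unequal shares, no true difference (70% in both arms).**

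- Restoration of 10% versus 30% of failures: 0.70/0.97 = 72.2% against 0.70/0.91 = 76.9%, a false difference of about 4.8 points in favour of the arm with more restorations.
- Exfoliation of 5% versus 10%: (0.10 − 0.05) × 0.30 = 1.5 points.

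**The case against.** The strongest reply is that the problem is small and partly answered elsewhere. Teeth nearing exfoliation are excluded at entry and follow-up is one year, so shedding may be rare; at 2% to 5% the loss is under one point. Exfoliation has no stated link to arm, and equal dilution is conservative for a superiority claim. The child-level outcome, read plainly, would not credit a lesion that was active at 6 months. Section 2.13 uses person-time for children who become non-compliant after 6 months, and Section 5 provides imputation and sensitivity analysis.

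Much of this limits the size. It does not remove the conflict. Section 2.8 itself foresees exfoliation, and its rule is unconditional. If the child-level outcome reads the other way, the two sections disagree. Section 2.13 concerns non-compliant children, and the imputation in Section 5 concerns dropouts; neither mentions a restored tooth in a child who still attends.

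Four stronger readings are tempting but not supported:

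- *All restored teeth are failures removed from view.* The rule covers restoration for whatever reason, so only some are. A lesion already found to extend past the dentine could still be scored as not arrested under 2.8.
- *The protocol drops restored lesions from the denominator.* It does not say so. This is the natural consequence of the named methods, and it remains an inference.
- *The trauma item contradicts itself.* The item sits under the not-arrested list, but its own words, "If the tooth is extracted due to fracture, trauma will not be counted for the study", read as exclusion. It is a misplaced bullet and no part of this point.
- *Restoration will differ by arm.* Nothing shows that it will. Arm 3's extra visits end at week 8, and all arms are assessed at 6 and 12 months.

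**Conclusion.** The point holds for the two stated rules. The exfoliation rule contradicts the probing criterion in the same section and does not fit the child-level outcome in Section 4. The restoration rule uses a concept that the named analyses cannot apply, and it does not separate restoration for active or progressing caries from other restoration, although extraction for progression is a failure.

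The direction under equal action is clear: higher arrest percentages and a smaller difference. Bias between arms is possible through unequal restoration, but the documents do not show it. The size cannot be settled from the documents. The figures above are illustrations resting on assumed shares, a 70% base rate for the unequal-restoration case and, for restoration, the assumption that the affected lesions are failures left without a result. Because the rules govern the primary outcome, they should be corrected before analysis.

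**What to change.** In Section 2.8, replace the two rules with scoring that Section 4 can use:

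1. Exfoliated tooth: not arrested if the last probing was active; arrested if the last probing was arrested; missing if never probed after baseline, and then handled by the imputation and sensitivity analysis in Section 5.
2. Restored tooth: record the reason. Restoration for active or progressing caries counts as not arrested; other restorations are missing and handled in the same way.
3. Delete the reference to censoring, and state that the same scoring applies to the tooth-level and child-level outcomes.
4. Keep the current rule as a sensitivity analysis, so that results remain comparable with the published definition.

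The cost is a few lines of outcome wording and one reason code on the case report form. Headline arrest percentages will be slightly lower. Scoring shed teeth by last probing also carries an observation forward, which has its own weakness: a lesion may change status between the last probing and exfoliation. The sensitivity analysis shows how much this matters. The change concerns scoring only and leaves treatment untouched.

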### 2.9. Secondary Outcome

To assess the children (and/or parents) satisfaction and acceptability and dentist factors associated with the use of the SDF. This will be assessed with the help of a self-reported questionnaire.

### 2.10. Participation Timeline

Each eligible child will be a part of the trial for one year from their baseline visit. The total number of visits depends on the study arms to which child is allocated (Figure 1).

### 2.11. Sample Size

The sample size was calculated based on the primary objective. In an exploration study [26], those children treated weekly with 38% SDF had a slightly higher proportion of arrested caries compared to annual application. There was no considerable difference in the proportion of caries arresting by either semiannual or annual application (less than 10%). We expect that the proportion of the arrested carious lesion not to be more than 14% between the two frequencies of application. Considering a slightly higher proportion of caries arrest by the four times application as compared to others, we estimated the sample size at the power of 0.80 and alpha error of 0.05 to be 120 per arm. Being a population (tribal), which is not mainstream and owing to the demands of multiple follows of the tribal population, it is expected that we could encounter a lost-to-follow-up of about 30%. Accordingly, the final sample size has been increased to 160 children per arm. In total, 480 children will be enrolled on the trial.

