There have been multiple clinical trials and several systematic reviews reporting the application of SDF causing the arrest of caries lesions in a high percentage of cases (30–70%) [16,17,18,19,20,21,22,23,24]. Nearly 70% of caries lesions in primary teeth would be expected to be arrested in two years after SDF application with the variation of annual or biannual application as compared to combined controls of 5% NaF varnish or restorations. According to the AAPD manual [25], nearly 68% (95% CI = 9.7 to 97.7) of cavitated caries lesions in primary teeth would be expected to be arrested in two years after SDF application with a variety of annual or biannual application as compared combined controls of 5% Sodium fluoride (NAF) varnish or restorations. The American Dental Association (ADA) guidelines recommend the use of 38% SDF twice a year application over 5% NaF varnish (once per week for 3 weeks application) to arrest the cavitated caries coronal lesions in primary and permanent teeth [16]. However, it is a conditional recommendation that implies that not all patients would benefit from the intervention and depends on individual risk for caries, preferences, values, etc.

Studies are comparing various frequencies (thrice a year, weekly, biannual, annual, five times weekly per year, etc.) of SDF; however, the evidence is inconsistent. A clinical trial has shown that the yearly application of SDF has a higher proportion of arrested caries compared to the weekly application [26]. Biannual application of SDF was found to be superior compared to annual application in arresting cavitated carious lesion [27,28,29,30,31]. Annual application of silver diamine fluoride prevented many more carious lesions than application of fluoride varnish four times per year [26,31].

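### The stated power of 0.80 is tied to the largest difference the protocol expects and to 120 children per arm that its own loss rate does not leave; 120 cannot be checked, and its one source is reported in opposite directions

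*Protocol article*

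**What the plan says.** Section 2.11 states its sizing result as "we estimated the sample size at the power of 0.80 and alpha error of 0.05 to be 120 per arm". Three statements lead up to it:

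- From reference 26, "those children treated weekly with 38% SDF had a slightly higher proportion of arrested caries compared to annual application".
- On the two less frequent schedules, "There was no considerable difference in the proportion of caries arresting by either semiannual or annual application (less than 10" per cent).
- On the difference expected in this trial, "We expect that the proportion of the arrested carious lesion not to be more than 14% between the two frequencies of application".

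The section also describes the expected advantage of the four-times schedule as slight. It allows for about 30% loss to follow-up and raises 120 to 160 per arm, 480 in all. It gives no reference arrest rate, no test and no sidedness.

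Section 1 describes the same reference the other way round: "A clinical trial has shown that the yearly application of SDF has a higher proportion of arrested caries compared to the weekly application [26". It also gives the only arrest rates in the document: "in a high percentage of cases (30–70" per cent) across trials and reviews, and about 70% and about 68% at two years.

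Section 4 states a directional hypothesis, that four applications are superior to the other frequencies.

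**The concern.** A power figure should belong to an effect that the investigators think plausible or the smallest worth detecting. Here it belongs to the top of the expected range, while the surrounding sentences describe effects that are slight or below 10 points. Quoted without its effect size, 0.80 then overstates what the trial can show over most of the effects it anticipates.

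Two further problems bear on the same figure. The inflation from 120 to 160 does not preserve 120 after the stated loss. And the only study cited as the basis for the calculation is reported with opposite results in two sections, so a reader cannot tell whether it supports an advantage for more intensive application.

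At stake is how a non-significant result is read. The protocol does not say it would conclude that the frequencies are equivalent, but a stated power of 0.80 invites that reading.

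**Working it through.** **Inputs.** Section 2.11: alpha 0.05, power 0.80, a difference of at most 14 points, 120 per arm, 160 enrolled per arm, about 30% loss. Section 1: arrest rates of 30-70%, about 68% and about 70%. Assumptions of this check: the cited rate is the lower arm, and there is one binary outcome per child.

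**Formulas** (two proportions, pooled variance under the null; d = p2 − p1, p̄ = their mean, q = 1 − p):

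- n = [z_α √(2p̄q̄) + z_β √(p1q1 + p2q2)]² / d²
- power = Φ{[d√n − z_α √(2p̄q̄)] / √(p1q1 + p2q2)}
- z_α = 1.960 two-sided or 1.645 one-sided; z_β = 0.842

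**Step 1: try to reproduce 120.** For 68% vs 82%, √(2 × 0.75 × 0.25) = 0.6124 and √(0.68 × 0.32 + 0.82 × 0.18) = 0.6043.

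- Two-sided: (1.960 × 0.6124 + 0.842 × 0.6043)² / 0.0196 = 149.
- One-sided: (1.645 × 0.6124 + 0.842 × 0.6043)² / 0.0196 = 117.2, so 118.

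Other reference rates:

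| Reference rate | n, 14 points, two-sided | n, 14 points, one-sided | Power at 120, 14 points, two-sided | Power at 112, 14 points, two-sided | Power at 112, 14 points, one-sided | Power at 120, 10 points, two-sided | Power at 120, 10 points, one-sided |
|---|---|---|---|---|---|---|---|
| 30% | 186 | 147 | 0.61 | 0.58 | 0.70 | 0.37 | 0.49 |
| 40% | 199 | 157 | 0.59 | 0.56 | 0.68 | 0.34 | 0.47 |
| 50% | 196 | 154 | 0.59 | 0.56 | 0.68 | 0.34 | 0.47 |
| 60% | 176 | 139 | 0.64 | 0.61 | 0.72 | 0.37 | 0.49 |
| 68% | 149 | 118 | 0.71 | 0.68 | 0.78 | 0.41 | 0.54 |
| 70% | 141 | 111 | 0.73 | 0.70 | 0.80 | 0.43 | 0.56 |

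Two-sided, a figure near 120 needs a reference rate of about 74-75% (74% vs 88% gives 123; 75% vs 89% gives 118).

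**Step 2: is 14 points the design difference?** The text does not say so outright. But at the cited rates a 10-point difference needs at least 229 per arm under every variant tried (one- or two-sided, pooled, unpooled or arcsine, with or without continuity correction). Of the stated differences, only 14 points can lead to about 120.

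**Step 3: smaller effects.** At 120 per arm, 10 points has power 0.34-0.43 two-sided and 0.47-0.56 one-sided. For 5 points the figures are 0.12-0.14 and 0.19-0.22. The loss of power does not depend on sidedness.

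**Step 4: loss to follow-up.** 120 / (1 − 0.30) = 171.4, so 172 per arm would preserve 120. The planned 160 matches a 25% loss (120 / 0.75 = 160). With 30% loss, 160 × 0.70 = 112. At 112, two-sided power for 14 points is 0.56-0.70.

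**Step 5: reference 26.** Section 2.11 has weekly application slightly above annual. Section 1 says "the yearly application of SDF has a higher proportion of arrested caries compared to the weekly application [26"]. Both cannot be right.

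**The case against.** Five points can be made for the protocol.

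**The 120 has possible derivations.** A one-sided 0.05 test at the cited 68% gives 118, and power is 0.808 at 120. Section 4's hypothesis is directional and no sidedness is stated. A three-arm chi-square test also gives 121 if the rates are 70/84/84, although the pattern Section 2.11 describes, with the two less frequent schedules close together (70/70/84), gives 140. A reader might infer that 120 matches no arrest rate in the document and is an arithmetical error. The document does not support that; it supports only that 120 cannot be checked.

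**The rates in Section 1 are background.** The 68% and 70% are two-year figures pooled over schedules, while this trial assesses at 6 and 12 months. A design rate of 74-75% lies inside the very wide interval printed with the 68% (9.7 to 97.7). This stands, and is why the results are given as a range.

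**The article is condensed.** The full protocol may hold the reference rate and sidedness. Their absence alone would be a weak point. But the ceiling wording, the shortfall at 30% loss and the two accounts of reference 26 are in the published text.

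**Several lesions per child add information.** This is the strongest objection, since Section 4 analyses surfaces and the per-child percentage arrested. Suppose 4 lesions per child and an intraclass correlation of 0.5 (both assumed). Then 112 children give an effective 112 × 4 / (1 + 3 × 0.5) = 179 per arm, and two-sided power for 14 points rises to 0.76-0.89. Section 2.11 does not use this, and even then 10 points has only 0.47-0.59. So low power at 14 points is not established, but the point about smaller effects survives.

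**Children lost after six months stay in the analysis** by imputation (Section 5). That keeps them in the denominator, but Section 2.11 sizes on children retained, and by that reckoning the number is 112.

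**Conclusion.** The concern holds in a limited form.

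- **Firm:** 14 points is worded as an upper bound, so at a fixed reference rate smaller effects have less power than at 14 points. A 30% loss from 160 leaves 112, not 120. Sections 1 and 2.11 contradict each other on reference 26.
- **Conditional on one binary outcome per child and reference rates of 30-70%:** two-sided power for 14 points is 0.59-0.73 at 120 and 0.56-0.70 at 112. One-sided, it is 0.68-0.80 at 112. That 14 points is the design difference is inferred from Step 2.
- **Not established:** a reader might infer that the trial is underpowered outright. The number of lesions per child and their correlation are unknown, so the document does not show that.
- **Also not established:** a reader might infer that alpha should be split because two comparators are named. Section 4's wording leaves open whether superiority over both or over either is required. If both are required, no adjustment is needed.

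The contradiction on reference 26 changes none of the figures above. It matters because it is the only study cited for the sizing.

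**What to change.** Keep 480 children and rewrite Section 2.11:

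1. Reconcile Sections 1 and 2.11 on what reference 26 found.
2. State the reference arrest rate, the test and its sidedness behind 120.
3. Replace the single power of 0.80 with a short table of power, or the detectable difference, at 112 evaluable children per arm for differences of 10 to 14 points. State what is assumed about lesions per child and their correlation.
4. Say that a non-significant comparison will be interpreted by its confidence interval, that is, by the differences the interval excludes.

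The cost is one rewritten paragraph and a power statement that is probably less favourable. No extra children, visits or data are needed.

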## 2. Methods

### 2.1. Study Design

This trial is designed as a randomized, controlled trial consisting of three parallel arms with an allocation ratio of 1:1:1 (Figure 1).

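### Enrolling 160 children per arm covers 25% loss, not the stated 30%: 112 remain instead of 120, and power falls from 80% to about 77%

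*Protocol article*

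**What the plan says.** The whole calculation is in section 2.11 of the protocol article. The base requirement is given as "we estimated the sample size at the power of 0.80 and alpha error of 0.05 to be 120 per arm". On the effect, the article says: "We expect that the proportion of the arrested carious lesion not to be more than 14% between the two frequencies of application". No arrest rate is given for any arm, and neither the test nor its sidedness is named.

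On attrition, citing the tribal population and the burden of repeated visits, it says "it is expected that we could encounter a lost-to-follow-up of about 30" per cent. The next sentence presents enrolment as the consequence of that expectation: "the final sample size has been increased to 160 children per arm". The total follows: "In total, 480 children will be enrolled on the trial". This agrees with section 2.1, which describes "three parallel arms with an allocation ratio of 1:1:1" (3 × 160 = 480). No inflation formula is shown.

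**The concern.** To keep a required number after a proportion d is lost, the requirement is divided by (1 − d). At 30% loss, 120 must be divided by 0.70, and 160 is visibly smaller than the result. The section therefore states a size, an attrition rate and a power that cannot all be true.

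This is the only justification given for enrolling 480 children. A reader would take it that 80% power survives the expected loss, and on the protocol's own figures it does not.

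**Working it through.** **Inputs, all from section 2.11:** required children per arm 120; power 0.80; alpha 0.05; expected loss about 30%; enrolled per arm 160.

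**1. Can the 160 be reproduced?**

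| Rule | Calculation | Result per arm |
|---|---|---|
| Divide by the retained fraction, 30% loss | 120 / 0.70 = 171.4 | 172 |
| Multiply by one plus the loss, 30% | 120 × 1.30 | 156 |
| Divide by the retained fraction, 25% loss | 120 / 0.75 | 160 |

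The correct rule at 30% gives 172 (check: 172 × 0.70 = 120.4), or 3 × 172 = 516 in total, which is 36 more than 480. The stated 160 is consistent with 156 rounded up, and it equals the 25% allowance exactly. The document does not say which route was taken, and the mismatch does not depend on it.

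**2. What does 160 leave?**

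- At 30% loss: 160 × 0.70 = 112 per arm. The shortfall is 120 − 112 = 8 per arm, or 24 over three arms.
- Largest loss that still leaves 120: 1 − 120/160 = 25%.

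**3. Power at 112.** Take the protocol's pairing of 120 with 80% as given. For a two-sided test at 0.05, the standardised effect at 120 is 1.960 + 0.842 = 2.802. It scales with the square root of the sample size:

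- at 112: 2.802 × √(112/120) = 2.707
- power = Φ(2.707 − 1.960) = Φ(0.747) = 77.2%

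The same scaling gives 77.6% for a one-sided test and 77.0% for an overall three-arm chi-square test on 2 degrees of freedom. The answer is about 77% in each case, and no base arrest rate is needed.

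**4. Cross-check with explicit rates (assumed, because the protocol gives none).** With a 14-point difference, a two-sided 0.05 test and no continuity correction, about 120 per arm is needed near 74.4% versus 88.4%. Power for that pair at 112 is 0.772. Neighbouring pairs bracket it:

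| Assumed rates | n for 80% power | Power at 120 | Power at 112 |
|---|---|---|---|
| 74% vs 88% | 123 | 0.793 | 0.765 |
| 75% vs 89% | 118 | 0.810 | 0.782 |

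Mirror-image low rates (11–12% vs 25–26%) give the same figures.

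**The case against.** Four points can be made for the plan.

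- **The loss figure is approximate.** It is worded as a possibility of about 30%. At 28% loss about 115 per arm remain, with power near 78%; at 25% nothing is lost. This stands as a comment on size. But the section gives reasons to expect heavy loss, and about 30% cannot be read as at most 25%.
- **Not every lost child drops out of the analysis.** Section 5 imputes values for dropouts after six months, and section 2.13 uses the person-time of children who become non-compliant after the first outcome assessment. Of the 48 children lost per arm at 30% (160 × 0.30), 8 late dropouts would bring the number analysed back to 120. This softens the shortfall but does not remove it. Section 2.13 withdraws children who become non-compliant before six months, and imputation does not restore full information. Section 4 also requires superiority in the per-protocol set as well as by intention to treat, and imputing in one set does not replace children missing from the other. Section 2.11 itself treats the loss as something to be met by more enrolment.
- **The 120 may contain slack.** A 14-point difference at 76% versus 90% needs only about 112 per arm. If a continuity correction was built into the 120, uncorrected power at 112 would be about 81–83%. The protocol mentions neither rounding up nor a correction, so this cannot be assumed. It is a fair reason to label the 77% as conditional.
- **The effect is small.** It is about 3 points of power, and only if the full 30% is lost. That is correct, and it is why the remedy should be light.

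**Conclusion.** The concern holds. With 160 enrolled and 30% lost, 112 children per arm remain rather than 120, and the planned enrolment protects 120 only up to 25% loss. That part is plain arithmetic on stated figures and needs no assumption.

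The power figure of about 77%, against the stated 80%, rests on two assumptions: that 120 per arm gives exactly 80%, and that lost children contribute nothing. The first cannot be verified without a base arrest rate. The second is somewhat pessimistic, given the planned imputation for late dropouts. The consequence is modest, but the sample-size statement is wrong as written and should be corrected.

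**What to change.** Keep 480 enrolled and correct the sentence in section 2.11 in one of two ways:

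- state that 160 per arm preserves 120 evaluable children at up to 25% loss to follow-up; or
- keep the 30% expectation and state that 112 per arm would then remain, with about 77% power under the same assumptions.

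Either costs one sentence and no extra children; under the second, the reported power is slightly less favourable. Holding both the 30% and the 120 would instead mean 172 per arm, 516 in total, which is 36 more children. A gain of about 3 points of power does not make that necessary.
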